#### Secondary outcomes

Secondary outcomes are the following:1) The rate of achieving ACR20, ACR50, ACR70 (Felson and LaValley, 2014). Measurement will be performed at every visit. Briefly, ACR20/ACR50/ACR70 is defined as a more than 20%/50%/70% improvement respectively in both tender joint count (TJC) and swollen joint count (SJC). Patients should simultaneously have a more than 20%/50%/70% improvement respectively in at least 3 items as follow: patient’s assessment of pain on a VAS, patient’s global assessment of disease activity, physician’s global assessment of disease activity, HAQ-DI and CRP level.2) Changes in TCM syndrome score. It will be evaluated based on the grading scales of RA symptoms required in the Guiding Principles of Clinical Research of New Chinese Medicine Treating RA (2002 Edition) issued by the National Medical Products Administration of China at every visit. The scores and details are presented in the Supplementary Material S4.3) Changes in VAS. Pain will be evaluated using a VAS at every visit according to a former study (Faiz, 2014).4) Changes in average hands grip strength. Measurement will be performed at every visit. The Jamar dynamometer is used to assess the hand grip strength (Higgins et al., 2018). For each strength test, three times of measurements should be done for each hand, and the mean score of both hands is recorded.5) Changes in HADS. Anxiety and depression will be evaluated at every visit according to a former study (Herrero et al., 2003).6) Changes in lumbar spine bone mineral density (L-BMD) to assess osteoporosis. Measurement will be performed at baseline and week 24.7) Changes in 7-joint ultrasound score (US7). Measurement will be performed at baseline and week 12, 24. It determines the severity of synovitis, synovial hyperplasia and bone erosion of 7 joints through color Doppler ultrasound semi-quantitative assessment (Backhaus et al., 2009). The scores and details are presented in the Supplementary Material S5.8) Consumption of concomitant medications. We will record any changes in the dose of NSAIDs or oral corticosteroids in the case report form (CRF). The drug name, total daily dose, and single dose will be record at every visit.

### Safety assessment

The interventions will be carried out under the guidance of a rheumatologist. The herbs in the KBXG are safe in accordance with the recommended amount in Chinese Pharmacopoeia. We will closely observe the physical conditions and subjective description of the participants. Blood, urine and stool routine analysis as well as liver and kidney function tests will be performed before enrollment and at 4, 8, and 12 weeks after enrollment. All adverse events will be recorded on the CRF and reported to the principal investigator. Any severe adverse events will be reported to the Ethics Committee of Xiyuan Hospital of China Academy of Chinese Medical Sciences within 24 h. The committee of medical experts will determine whether adverse events are related to the KBXG. Xiyuan Hospital of China Academy of Chinese Medical Sciences will cover the cost of treatment and the corresponding economic compensation for the damage related to the trial. Participants have the right to withdraw their consent to participate in the study at any time for any reason. Other unintended effects of study interventions and study conduct will also be recorded and reported.

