## Methods

### Trial design

This is a single-center, randomized, double-blind, parallel group, placebo-controlled clinical trial. The trial will be conducted in the Xiyuan Hospital of China Academy of Chinese Medical Sciences. A total of 90 eligible female participants will be randomized into the experimental group (KBXG) or the control group (placebo) with a 1:1 ratio. Two groups will continue their original treatment regimen during the trial. The duration of the intervention is 12 weeks, and follow-up is 12 weeks. Study visits will take place at baseline and at 4, 8, 12, 24 weeks. Every patient will be asked to visit within 3 days of the given time point. All participants will be required to sign the written informed consent before randomization. This protocol was compiled in line with the Standard Protocol Items: Recommendations for Interventional Trials (SPIRIT) Guidelines (Chan et al., 2013), which is presented in the Supplementary Material S1. The flowchart of this trial is presented in Figure 1.

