### Participant timeline

The schedule of enrollment, interventions, and assessments is as shown in Table 2.

**TABLE 2 T2:** A standard protocol items: recommendation for interventions for trials (SPIRIT).

	Study period						
	Enrollment	Allocation		Post-allocation			Follow up
Time point	- Day 3	Day 0	Week 0	Week 4	Week 8	Week 12	Week 24
Enrolment							
Eligibility screen	X						
Informed consent	X						
Allocation		X					
Interventions							
KBXG			X	X	X	X	
Placebo			X	X	X	X	
Assessments							
DAS28-CRP	X			X	X	X	X
CDAI			X	X	X	X	
ACR20/50/70			X	X	X	X	
TCM syndrome score			X	X	X	X	X
VAS			X	X	X	X	X
Average hands grip strength			X	X	X	X	X
HADS			X	X	X	X	X
L-BMD			X				X
US7			X			X	X
Consumption of concomitant medications	X		X	X	X	X	
ESR, CRP	X			X	X	X	X
Blood routine	X					X	X
Urine routine	X					X	X
Stool routine	X					X	X
Liver and kidney function	X					X	X
AEs			X	X	X	X	

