### Sample size

The sample size is calculated based on the primary endpoint (the changes in DAS28-CRP). According to the previous exploratory clinical trial (unpublished), the effect size of the treatment group was 83.9%, with a power of 0.9 and alpha of 0.05, a total of 68 female patients should be included to determine an increase of 15% in disease activity improvement between the KBXG and placebo groups. To account for a 20% loss to follow-up, at least 85 female patients will be required in this trial. Thus, a total of 90 female patients (45 female patients in each group) are planned to be enrolled.

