### Data monitoring, harms and auditing

The Data Monitoring Committee (DMC) of Xiyuan Hospital of China Academy of Chinese Medical Sciences will meet once half a year to review trial conduct. The committee will conduct primary outcome interim analyses to oversee the safety and efficacy of the study when it reaches 50% of the recruitment. Besides, the committee will assess the status and quality of the study and make recommendations to continue or terminate the study. KBXG is relatively safe, and AEs are mild. Every patient could report any AEs to the researchers *via* phone and the researchers would immediately take action.

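### The safety text schedules laboratory tests at Weeks 4, 8 and 12, but Table 2 marks them only at Day -3, Week 12 and Week 24

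*Protocol article*

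**What the plan says.** The Safety assessment section names the panel and its first time point: "Blood, urine and stool routine analysis as well as liver and kidney function tests will be performed before enrollment". The same sentence then gives the full list of times: "liver and kidney function tests will be performed before enrollment and at 4, 8, and 12 weeks after enrollment". It sets no Week 24 test.

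The Participant timeline section presents Table 2 as the schedule of assessments. Its rows for blood routine, urine routine, stool routine and "Liver and kidney function" are all marked at Day -3, Week 12 and Week 24. Their Week 4 and Week 8 cells are blank.

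The Trial design section says "Study visits will take place at baseline and at 4, 8, 12, 24 weeks", so every time point in either list is a planned visit.

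On adverse events, the Safety assessment section says "All adverse events will be recorded on the CRF and reported to the principal investigator" and gives no end date. The AE row of Table 2 runs from Week 0 to Week 12, with no mark at Week 24.

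**The concern.** Two current parts of the same document set different schedules for the same tests, and a site cannot follow both.

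The difference falls in the treatment period. Under Table 2, a symptom-free fall in blood count or rise in liver or kidney markers would first be found by a protocol test at Week 12, when dosing with the granules ends and stopping them is no longer an option. Under the inclusion criteria, every participant takes methotrexate or leflunomide throughout, and the KBXG arm adds a 12-herb product. Safety is one of the trial's two stated aims.

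The choice also affects the safety result. The Statistical methods section compares AE incidence between groups, and events detected by laboratory tests can be counted only when a test is done. The Data Monitoring Committee's safety review at 50% recruitment would likewise have no Week 4 or Week 8 laboratory data.

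**Working it through.** No power, sample size or alpha figure is involved. The check sets the text against the table and counts the consequences.

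**1. The two lists.** Table 2 has seven time columns: Day -3, Day 0, Week 0, Week 4, Week 8, Week 12 and Week 24.

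| Time point | Safety assessment text | Table 2, four laboratory rows |
|---|---|---|
| Before enrolment (Day -3) | yes | yes |
| Week 4 | yes | no |
| Week 8 | yes | no |
| Week 12 | yes | yes |
| Week 24 | no | yes |

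They agree on the pre-enrolment and Week 12 tests and disagree on the other three.

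**2. Is it a shifted or broken table?** Rows that can be checked against other text are in the right place. For US7, the Secondary outcomes section says "Measurement will be performed at baseline and week 12, 24", and the table marks Weeks 0, 12 and 24. For L-BMD, the same section gives baseline and Week 24, and the table marks Weeks 0 and 24. The ESR/CRP row, directly above the laboratory rows, carries marks at Day -3 and Weeks 4, 8, 12 and 24. All four laboratory rows show the same pattern. A column shift does not explain this.

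**3. Panels per patient, Week 4 to Week 12.** Text: Weeks 4, 8 and 12 = 3. Table 2: Week 12 = 1.

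**4. Longest on-treatment interval without a panel.** Text: 4 weeks. Table 2: about 12 weeks, from baseline to the end of dosing.

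**5. Panels at stake over the whole trial.**
- If Table 2 governs and all 90 attend: 2 visits × 90 = 180 panels at Weeks 4 and 8 are not done.
- The Sample size section plans "To account for a 20% loss to follow-up". If all of that loss fell before Week 4 (an assumption, since timing is not given): 90 × 0.8 = 72 attend, and 2 × 72 = 144 panels are not done.
- If the text governs, none of these is missed, but the Week 24 panel in Table 2 (72 to 90 panels) is not scheduled.

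**The case against.** The strongest counter-argument is that Table 2 is probably just incomplete. Other rows lack marks that the text requires. The Outcomes and measurements section puts CDAI and ACR20/50/70 at every visit and records concomitant medication at every visit, yet none of these rows is marked at Week 24. Omitted Week 4 and Week 8 laboratory marks are therefore at least as plausible as a deliberate plan to skip the tests, and sites may be working from the text, or from a full protocol and CRF (not shown) that hold one consistent list. This stands as a reason not to assume that the tests will be missed. It does not remove the conflict: the article calls Table 2 the schedule, and no statement gives the text precedence.

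The harm should also be kept in proportion. ESR, CRP and AE recording continue at Weeks 4 and 8 under either reading, a rheumatologist oversees treatment, background csDMARD doses are stable and serious organ disease is excluded. A Week 12 abnormality could still change background therapy, so the lost opportunity concerns the study granules. The trial-wide panel counts include the placebo arm. These points limit the concern to abnormalities that only a laboratory test would show, but none replaces interim tests of the added product.

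The missing Week 24 AE mark is a side note. It does not show that AE recording stops at Week 12, because the text sets no time limit and the Data monitoring section adds "Every patient could report any AEs to the researchers".

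**Conclusion.** The contradiction is real and should be fixed. Text and table disagree at Weeks 4, 8 and 24, and the article does not resolve it. If Table 2 is followed, post-baseline panels by Week 12 fall from three to one per patient, and the longest on-treatment gap rises from 4 to about 12 weeks. Trial-wide, 144 to 180 panels would not be done, the lower figure resting on the assumption that all planned loss falls before Week 4. If the text is followed, no on-treatment panel is lost, but the Week 24 panel is unscheduled.

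This is a matter of safety monitoring and of which laboratory events can be observed. The primary analysis and power are unaffected, and no between-group bias is claimed because both arms follow the same schedule.

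**What to change.** State one list in both places. The recommended list is Day -3 and Weeks 4, 8, 12 and 24.

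- **Table 2:** add Week 4 and Week 8 marks to the four laboratory rows (4 × 2 = 8 cells).
- **Week 24, if intended:** add it to the Safety assessment sentence and mark the AE row at Week 24. That makes one sentence and 8 + 1 = 9 cells in all.
- **Week 24, if not intended:** leave the sentence as it is and delete the Week 24 mark from the four rows (8 additions and 4 deletions). A panel 12 weeks after the last dose is the sponsor's decision; the document does not settle it.

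Compared with following Table 2, the cost is two extra panels per patient, including urine and stool samples, at visits that already take place and where blood is already drawn for ESR and CRP. If the full protocol v3.0 or the CRF carries the same conflict, correct it there too. The Ethics and dissemination section requires the ethics committee's agreement before significant changes, so if v3.0 omits the Week 4 and Week 8 tests, adding them may need that agreement first and not only a notification.

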### Participant timeline

The schedule of enrollment, interventions, and assessments is as shown in Table 2.

**TABLE 2 T2:** A standard protocol items: recommendation for interventions for trials (SPIRIT).

	Study period						
	Enrollment	Allocation		Post-allocation			Follow up
Time point	- Day 3	Day 0	Week 0	Week 4	Week 8	Week 12	Week 24
Enrolment							
Eligibility screen	X						
Informed consent	X						
Allocation		X					
Interventions							
KBXG			X	X	X	X	
Placebo			X	X	X	X	
Assessments							
DAS28-CRP	X			X	X	X	X
CDAI			X	X	X	X	
ACR20/50/70			X	X	X	X	
TCM syndrome score			X	X	X	X	X
VAS			X	X	X	X	X
Average hands grip strength			X	X	X	X	X
HADS			X	X	X	X	X
L-BMD			X				X
US7			X			X	X
Consumption of concomitant medications	X		X	X	X	X	
ESR, CRP	X			X	X	X	X
Blood routine	X					X	X
Urine routine	X					X	X
Stool routine	X					X	X
Liver and kidney function	X					X	X
AEs			X	X	X	X	

### Sample size

The sample size is calculated based on the primary endpoint (the changes in DAS28-CRP). According to the previous exploratory clinical trial (unpublished), the effect size of the treatment group was 83.9%, with a power of 0.9 and alpha of 0.05, a total of 68 female patients should be included to determine an increase of 15% in disease activity improvement between the KBXG and placebo groups. To account for a 20% loss to follow-up, at least 85 female patients will be required in this trial. Thus, a total of 90 female patients (45 female patients in each group) are planned to be enrolled.

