### Outcomes and measurements

#### Primary outcome

The primary outcomes are the change in DAS28-CRP and CDAI at every visit.

The DAS28-CRP is widely used as an indicator of RA disease activity and response to treatment, and clinical trials have used DAS28 to assess treatment effect (Gardiner et al., 2005; Jain et al., 2021; Zhang et al., 2022). A change of ≥1.2 score is considered clinically significant difference (Van Gestel et al., 1998). The DAS28-CRP is calculated as DAS28-CRP = 0.56*sqrt (TJC28) + 0.28*sqrt (SJC28) + 0.36*ln (CRP+1) + 0.014*VAS +0.96 (van Riel, 2014).

The CDAI is calculated as CDAI = TJC28 + SJC28 + overall disease activity on a 0–10 VAS completed by the patient + overall disease activity on a 0–10 VAS completed by the physician (Aletaha et al., 2005). High disease activity is defined as a CDAI >22, moderate activity as a CDAI >10 and ≤22, low activity as a CDAI >2.8 and ≤10, and remission as a CDAI ≤2.8.

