## Discussion

RA is a chronic inflammatory disease with high morbidity and mortality. It is reported that the life expectancy of RA patients is usually 6–11 years less than that of normal people. Notably, the majority of them are females (Cush, 2021). Moreover, disease activity, radiographic damage and physical disability of female RA patients are more severe than that of male (Kuiper et al., 2001). Recurrent joint pain, progressive joint deformation and even disability have a substantial effect on female patients’ physical and mental health. Due to the side effects of conventional drugs, the choices of treatment of female RA patients are also conditioned during childbearing age, pregnancy, and lactation. Thus, the optimal treatment regimen for female RA patients should be carefully considered.

As a complementary and alternative medicine, TCM is widely used in RA treatment in China, which has shown the effects of reducing disease activity, improving clinical symptoms, and enhancing the quality of life. In our previous small sample exploratory clinical study, we found that compared with hydroxychloroquine sulfate, KBXG significantly improved clinical symptoms and joint function, reduced disease activity and the level of inflammation factors of female RA patients. At the same time, no adverse events (AEs) occurred (Niu, 2020). Therefore, it is necessary to conduct standardized randomized controlled clinical trials to confirm the efficacy and safety of KBXG.

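### The sample size paragraph names a continuous endpoint but uses two percentages, and these do not support 68 patients in total for 90% power

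*Protocol article*

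**What the plan says.** The Sample size section opens with the endpoint: "The sample size is calculated based on the primary endpoint (the changes in DAS28-CRP"). It then gives the inputs, "the effect size of the treatment group was 83.9%, with a power of 0.9 and alpha of 0.05", and the result, "a total of 68 female patients should be included to determine an increase of 15% in disease activity improvement". An allowance of 20% for loss raises 68 to 85, and the plan rounds this to 90, or 45 per arm.

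Three other sections bear on this:

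- Primary outcome defines DAS28-CRP as a continuous score and says of it: "A change of ≥1.2 score is considered clinically significant difference". CDAI is a second primary outcome.
- Statistical methods plans analysis of covariance on changes from baseline, with two-sided testing at 0.05.
- Randomization and allocation fixes a 1:1 ratio.

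**The concern.** A sample size for a difference in mean change needs a mean difference and an SD, or their ratio. The paragraph gives neither. It gives one percentage described as belonging to the treatment group and a second described as "an increase of 15% in disease activity improvement between the KBXG and placebo groups". The pair looks like response proportions, which belong to a different endpoint and a different test.

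The figure of 90% is the only justification offered for the size of the trial. If it does not follow from its inputs, a null result could be read as strong evidence against a 15% benefit that the calculation never showed the trial could detect.

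**Working it through.** **Inputs.** From Sample size: 83.9%, 15%, power 0.90, alpha 0.05, 68 in total (34 per arm), 20% loss, 90 enrolled (45 per arm). From Statistical methods: two-sided. From Randomization and allocation: 1:1. The normal quantiles are 1.960 and 1.2816.

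**The step that reproduces.** 68 / (1 − 0.20) = 85. After 20% loss, 90 × 0.80 = 72, or 36 per arm.

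**Reading A: response rates, 83.9% against 68.9%.** The second rate is implied (83.9 − 15), not stated.

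- Sum of variances: 0.839 × 0.161 + 0.689 × 0.311 = 0.3494. Mean rate 0.764, so 2 × 0.764 × 0.236 = 0.3606.
- Pooled formula: n per arm = [1.960 × √0.3606 + 1.2816 × √0.3494]² / 0.15² = 166.3, so 167 per arm and 334 in total.
- Unpooled formula: n per arm = (1.960 + 1.2816)² × 0.3494 / 0.15² = 163.1, so 164 per arm and 328 in total.
- Power at n per arm (pooled) = Φ[(0.15√n − 1.960 × √0.3606) / √0.3494].

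| Per arm | Pooled | Unpooled |
|---|---|---|
| 34 | 30.5% | 31.6% |
| 36 | 32.0% | 33.1% |
| 45 | 38.6% | 39.8% |

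One-sided testing raises power at 34 per arm only to 42%.

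**Reading B: response rates upward, 98.9% against 83.9%.** The same formulas give 71.3 (pooled) or 68.2 (unpooled) per arm, so 69 to 72 per arm. Power at 34 per arm is 60 to 63%.

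**Reading C: 15% as a relative difference in rates.** A lower placebo rate (0.839/1.15 = 0.730, or 0.839 × 0.85 = 0.713) needs 590 or 458 in total. An upward change to 0.839 × 1.15 = 0.965 needs 232.

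**Reading D: 83.9% as a standardised difference of 0.839.** A two-sided t-test needs 30.8 per arm, so 62 in total. Power at 34 per arm is about 93%, but the 15% plays no part.

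**Reading E: 15 points as a difference in mean percentage improvement.** At 34 per arm, a two-sided t-test has 90% power for a standardised difference of 0.798, so 68 in total requires an SD of 15 / 0.798 = 18.8 points. The paragraph states no SD, and 83.9% plays no part. Power at 34 per arm for assumed SDs:

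| Assumed SD (points) | Power |
|---|---|
| 15 | 98% |
| 20 | 86% |
| 25 | 68% |
| 30 | 53% |

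**What the trial can detect on its stated endpoint.** For a two-sided t-test at 90% power, the detectable standardised difference is 0.798 at 34 per arm, 0.775 at 36 and 0.691 at 45. If the SD of DAS28-CRP change is 1.0 to 1.5 (an assumption; the document gives none), 0.775 corresponds to 0.775 × 1.0 = 0.8 up to 0.775 × 1.5 = 1.2 points.

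**The case against.** The strongest objection is that the power of about one third depends on a reading the text does not state. The paragraph never speaks of responders or a response rate, never gives 68.9%, and names a continuous change as its basis. Comparing proportions is not the planned primary analysis; the only efficacy rates to be compared are the ACR rates. Reading E also shows that a continuous calculation using the 15% can give 68. All of this stands. A reader might infer that the trial has about 30% power, or that it would miss a real benefit two times in three. The document does not support that as a statement about the planned analysis, which may be well powered for a large standardised difference.

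Two further inferences should not be drawn. First, 68 might be a per-arm figure entered as a total (Reading B, unpooled, gives 68.2), or it might come from a one-sample, one-sided test of 83.9% against 68.9% (67.5). The text supports neither origin. Second, the Discussion describes an exploratory study in which, "compared with hydroxychloroquine sulfate, KBXG significantly improved clinical symptoms and joint function". It is tempting to conclude that 83.9% is therefore not a placebo-controlled effect. But Sample size calls its source unpublished, while the Discussion cites its study, and nothing says the 83.9% came from that comparison. The Discussion also concedes that relying on the earlier study may overestimate efficacy.

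The objection does not rescue the paragraph. No reading uses both percentages and gives 68 in total for a two-arm comparison. The readings that come close each drop one input, and Reading E also needs an SD that is not given.

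**Conclusion.** The point holds in this form: the stated 90% power is not supported for the stated 15% difference, and the power of the planned analysis of covariance cannot be determined from the text. The mismatch between endpoint and inputs is certain, because it is visible in the paragraph itself.

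The size of the shortfall is conditional. It is about 30 to 32% power at 34 per arm if the inputs are 83.9% and 68.9% response rates tested two-sided, and 60 to 63% if they are 98.9% and 83.9%. Under the continuous readings, power depends on an unstated SD or leaves the 15% unused. Only the dropout step is confirmed. The full protocol might state an SD, but the paragraph presents its chain of figures as complete, and that chain does not close.

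**What to change.** Keep N = 90. Remove the 83.9% and 15% as the basis, or say what they are; if they are response rates, state that power for a 15-point difference is about one third.

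Restate the paragraph on the primary endpoint along these lines: with 90 randomised and about 72 evaluable after 20% loss (36 per arm), the trial has 90% power at two-sided 0.05 to detect a standardised difference of about 0.78 in DAS28-CRP change (0.80 at 34 per arm), before any allowance for the second primary outcome (CDAI) or the interim efficacy analysis. The value should be 0.78 rather than 0.77, since 0.77 at 36 per arm gives 89.6%.

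Name the visit to which this applies, because the Primary outcome section refers to every visit. Give the assumed SD with its source, and the implied difference in points (about 0.8 to 1.2 if the SD is 1.0 to 1.5), so that readers can set it beside the 1.2-point change in that section. Present it as a detectable difference, since it is solved from a fixed N.

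The cost is wording only, with no extra patients. The drawback is that the stated figure becomes less favourable.
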